### Analysis plan

Since the number of clusters is small, we will use a fixed effects linear regression model to assess the effect of the intervention. The outcome variable will be number of cigarettes/day at 8 weeks, 20-weeks and 32-weeks. Baseline number of cigarettes/day will be included as a covariate. We will include a fixed effect for treatment centre, which accounts for differences in the average level of the outcome across centres and the association between before/after and centre induced by the stepped-wedge design. The main predictor of interest will be a before/after intervention variable, which would be at a different time point for each centre and will measure the intervention effect, which after adjusting for centre is a weighted average of the effect within each centre. Time will be included in the model as a continuous measure to account for any secular trends. We will use boot-strapped estimates of the standard error to account for any violations in the assumption of normality of residuals. The data will be analysed following the intent-to-treat principle. The primary analysis will be a complete case analysis, with sensitivity analysis undertaken to include all participants under an appropriate model for missing data such as multiple imputation. Analysis will be conducted independently by statisticians in the Clinical Research Design, IT and Statistical Support Unit, University of Newcastle.

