## Methods/Design

### Study setting

The research program is being conducted at four residential alcohol and other substance abuse treatment programs: The Salvation Army William Booth House (102 beds, including 82 for males and 20 for females), The Salvation Army Blue Mountains Recovery Services (22 beds for males), The Salvation Army Canberra Recovery Services (44 beds, including 36 for males and 8 for females), and The Salvation Army Dooralong Transformation Centre (125 beds, including 85 for males and 40 for females). The treatment program across each of these sites is up to 10-months in length and is operated in the form of a modified therapeutic community. The Bridge Program aims to provide a whole of life, person-centred and coordinated care approach to recovery. Its incorporates group work, case management, one to one support, spiritual support, health care, chapel services, recreational and social activities, family involvement and employment training. The program uses a range of therapeutic approaches including motivational enhancement strategies, 12 Step Model of Recovery, Cognitive Behavioural Therapy, Case Management and Vocational Education and Training. Previous research has described these programs and examined the characteristics of people accessing these services (e.g. [4,25-28]).

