### Interventions

#### Treatment condition (Healthy Recovery)

In addition to completing treatment as usual, participants in the Treatment Condition will complete Healthy Recovery. Healthy Recovery is an 8-session group based healthy lifestyle intervention that was developed for people attending residential substance abuse treatment. It is delivered over a 5-week period, with two groups being conducted each week for the first 3-weeks, and then 1 group a week conducted during the next two weeks. The first group session is completed over 90 minutes, with subsequent group sessions completed over 60 minutes. Healthy Recovery focuses on helping participants to reduce their smoking, increase their intake and variety of fruit and vegetables, and increase their level of physical activity. The intervention involves a combination of health focused psycho-education, goal setting, monitoring, motivational interviewing, and cognitive behavioural therapy. Participants are provided with pedometers to monitor their steps and these are used as a motivational tool for participants. Contingency management is also used to promote reductions in smoking. Participants will have an opportunity to earn up to $60 AUD over the course of the 5-week program if they are able to successfully reduce their smoking. Contingency management payments will be based on reductions from baseline expired carbon monoxide (CO) scores using a smokerlyzer (Micro Smokerlyzer®; Bedfont Technical Instruments Ltd, Kent, UK). In weeks 2 and 3 participants will have an opportunity to earn $5 AUD for any reductions in their CO score, $7 for halving their CO score and $15 for demonstrating that they have quit smoking. In weeks 4 and 5 participants are only rewarded for halving their CO score or quitting smoking. If smoking at least 10 cigarettes per day, participants are recommended to commence nicotine replacement therapy (NRT). If required, the NRT will be prescribed to participants by the general practitioner that attends the treatment program. Costs associated with NRT are subsidised under the Australian Pharmaceutical Benefits Scheme. The group sessions will be co-facilitated by a Salvation Army drug and alcohol worker and a member of the research team (i.e. Intern Psychologist or Clinical Psychologist). To track adherence to the intervention, group attendance logs are maintained (participants are trained to complete these logs during groups sessions). Participants are also asked to log their health behaviours each day onto a worksheet (i.e. number of cigarettes, servings of fruit and vegetables, steps walked, minutes of exercise). These worksheets are photocopied by the research staff and kept to monitor adherence.

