### Data analysis

#### Power analysis

The primary outcome is number of cigarettes/day at 8 weeks follow-up. Unpublished pilot data suggests this has a SD of 12 cigarettes/day. Assuming a baseline/follow-up correlation of 0.25 we would need a sample of 85 before and 85 after intervention to give the study 80% power to detect a 5 cigarette/day intervention effect at a 5% significance level. We have added another 15% to allow for non-parametric distribution of the data, i.e. 98 people before and after. To account for loss to follow-up we have added another 40% (based on previous RCTs conducted by the researchers), providing a sample of about 140 people who will complete before and after measures.

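### The primary model has no term for correlation within site-by-step cohorts and the bootstrap is aimed only at non-normality, so the 8-week standard error is too small whenever that correlation is above zero

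*Protocol article*

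**What the plan says.** The Analysis plan section of the protocol article chooses the model because there are few sites: "Since the number of clusters is small, we will use a fixed effects linear regression model to assess the effect of the intervention". Study setting gives the number: "The research program is being conducted at four residential alcohol and other substance abuse treatment programs". Centre enters as a fixed effect: "We will include a fixed effect for treatment centre, which accounts for differences in the average level of the outcome across centres". The intervention effect is a before/after variable that switches at a different point in each centre. Baseline consumption is a covariate, and calendar drift is handled by one linear term: "Time will be included in the model as a continuous measure to account for any secular trends". The only statement on standard errors is "We will use boot-strapped estimates of the standard error to account for any violations in the assumption of normality of residuals". No participant term, site-by-step term, cluster-robust variance or resampling unit is named.

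The two statistical sections differ on the outcome. Power analysis says "The primary outcome is number of cigarettes/day at 8 weeks follow-up". Analysis plan says "The outcome variable will be number of cigarettes/day at 8 weeks, 20-weeks and 32-weeks".

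Study design has participants recruited at every site at each step, and gives high interaction between residents as the reason for not randomising individuals. Interventions adds that "Healthy Recovery is an 8-session group based healthy lifestyle intervention", co-facilitated by a site worker and a member of the research team.

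**The concern.** A fixed centre effect takes out only what is constant at a site over the whole study. People enrolled at one site in one step also share a mix of residents, staff and house norms at that time and, under treatment, one run of group sessions and one pair of facilitators. Their outcomes may therefore move together around the centre mean and the linear trend. The before/after variable is the same for everyone in such a cohort, so this shared variation goes straight into the error of the treatment estimate, while the regression counts each person as separate information. A bootstrap meant to deal with the shape of the residuals does not address this unless it resamples whole cohorts.

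This is the primary efficacy test. Intervals that are too narrow make it more likely that a chance difference is read as an effect of Healthy Recovery, and the abstract proposes wider dissemination if the program is shown to be effective.

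**Working it through.** **1. Reproduce the stated sample size.** Inputs from Power analysis: SD 12, baseline/follow-up correlation 0.25, difference 5, power 80%, significance 5% (two-sided assumed). Residual SD = 12 × √(1 − 0.25²) = 11.62. Number per condition = 2 × (1.960 + 0.842)² × 11.62² / 5² = 84.8, so 85, as stated. Then 85 × 1.15 = 97.75 (98 stated) and 98 × 1.40 = 137.2 (about 140 stated). The figure is reproduced with independent observations and no design effect; the two inflations are for non-normality and loss to follow-up.

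**2. Assumed inputs.** The documents as shown give no cohort ICC, no correlation between follow-up visits and no number of steps (the design figure is not reproduced). Assumed: 4 sites × 5 steps = 20 equal cohorts; cohort ICC 0.01 to 0.10; visit-to-visit correlation ρ 0.25 to 0.7. Cohort size n runs from 98/20 ≈ 5 (if 98 is the total analysed) to 196/20 ≈ 10 (if 98 is per condition).

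**3. Week 8 only, one row per person.** Centre, time and before/after are all constant within a cohort. With equal cohorts the true standard error therefore exceeds the independent-row one by about √(1 + (n − 1) × ICC), and the actual error of a nominal 5% test is 2 × [1 − Φ(1.96 / ratio)].

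| Cohort ICC | n = 5: ratio, error | n = 10: ratio, error | Simulated error, n = 5-10 |
|---|---|---|---|
| 0.01 | √1.04 = 1.02, 5.5% | √1.09 = 1.04, 6.0% | about 5.5-6% |
| 0.05 | √1.20 = 1.10, 7.4% | √1.45 = 1.20, 10.4% | about 7.5-10.5% |
| 0.10 | √1.40 = 1.18, 9.8% | √1.90 = 1.38, 15.5% | about 10-17% |

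The last column comes from simulating the planned regression under no intervention effect. With ICC 0 the simulated error was close to 5%, so the excess comes from the cohort correlation.

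**4. If the three follow-ups are pooled without a participant term.** With no cohort effect the ratio is √(1 + 2ρ):
- ρ = 0.25: √1.5 = 1.22, error 11%
- ρ = 0.5: √2.0 = 1.41, error 17%
- ρ = 0.7: √2.4 = 1.55, error 21%

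Simulation gives about 11-22%. With cohort ICC 0.05 the ratio is √(1 + 2ρ + 3(n − 1) × 0.05). It runs from √2.1 = 1.45 (ρ 0.25, n = 5; 18%) to √3.75 = 1.94 (ρ 0.7, n = 10; 31%). Simulation gives about 15-30%. Clustering the standard error on the person restores about 5-6% when there is no cohort effect, but leaves about 7-14% with cohort ICC 0.05.

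**5. Effect on the stated power.** In the plan's own calculation the standard error is 11.62 × √(2/85) = 1.782, and 5/1.782 = 2.806. With 170 analysed in 20 cohorts, n = 8.5. Power is Φ(2.806/ratio − 1.96):
- ICC 0.01: ratio √1.075 = 1.037, power 77%
- ICC 0.05: ratio √1.375 = 1.173, power 67%
- ICC 0.10: ratio √1.75 = 1.323, power 56%

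This changes the cohort correlation only and leaves every other simplification in that calculation as it stands.

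**The case against.** Two stronger readings are tempting.

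The first is that the plan treats every outcome value as independent and ignores clustering. The text does not support that. The authors considered the small number of sites and chose a fixed centre effect, which removes stable between-site correlation; baseline and linear time take out more. What is left is the residual correlation within a site and step.

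The second is that the primary test certainly stacks three values per person, so that the larger error rates describe the primary analysis. The power section names week 8 alone, the model has no visit or treatment-by-visit term, and its time variable is there for secular trend. Three separate regressions would fit that description. The sentence listing all three times as the outcome reads most naturally as one model, but it does not settle the matter. The repeated-row figures are therefore conditional.

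The resampling unit is also unstated, and a condensed article may leave it to the full analysis plan; resampling participants or cohorts is not ruled out. That is fair. However, the stated purpose is non-normality only, and resampling participants would still leave the cohort correlation uncovered.

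Finally, the ICC, the number of steps and equal cohorts are all assumed, although the sites range from 22 to 125 beds. With a small ICC the week-8 excess is slight. This limits the size of the point but not its direction.

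**Conclusion.** The concern holds in limited form. The protocol fixes a model that accounts for stable centre differences and linear drift, and gives the bootstrap a different job. Correlation within site-by-step cohorts is left uncovered in a trial whose own description makes such correlation plausible.

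For the 8-week outcome the excess runs from negligible (about 5.5-6% at ICC 0.01) to material (about 10-17% at ICC 0.10). It becomes serious only if the three follow-ups are pooled without a participant term. That cannot be decided until Power analysis and Analysis plan are reconciled. All sizes rest on the assumed layout and correlations. This should be fixed before analysis, but it does not by itself invalidate the design.

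**What to change.** 1. Reconcile Power analysis with Analysis plan. Either state that the primary test uses week 8 only, with weeks 20 and 32 fitted separately as secondary, or specify one repeated-measures model with visit and participant terms.
2. Keep centre as a fixed effect and add a random site-by-step cohort effect, with Kenward-Roger or Satterthwaite degrees of freedom. Alternatively keep the bootstrap, but name its unit: whole site-by-step cohorts, with all rows of a participant kept together. In a null check at week 8, resampling whole cohorts held the error at about 3-5%.
3. Do not resample the four sites themselves; four units are too few for a reliable bootstrap.
4. Restate power over a range of assumed cohort ICCs, since the stated 80% contains no design effect.

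Data collection does not change; the work is analysis wording and code. The price is wider intervals and an acknowledged power below 80% if the sample size stays as planned.

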## Discussion

It is common for people accessing substance abuse treatment to smoke cigarettes, have poor dietary habits and engage in low levels of physical activity [4]. In conjunction with their extensive history of alcohol and other substance abuse, these unhealthy behaviours increase the risk of this population developing cardiovascular disease, cancer and other lifestyle related chronic diseases. There is an opportunity for substance abuse treatment providers to address smoking and other health behaviours as part of routine care. The present study aims to examine the effectiveness of ‘adding’ Healthy Recovery, a group based healthy lifestyle intervention, to residential alcohol and other substance abuse treatment. It is expected that when compared to the control condition, participants completing Healthy Recovery will demonstrate greater reductions in the number of cigarettes that they smoke each day. It is also expected that there will be greater increases in their intake and variety of fruit and vegetables, overall diet quality and their level of physical activity. As the current study is the first randomised controlled trial of a healthy lifestyle intervention within residential substance abuse populations, the results potentially hold important implications for the way that multiple health risk behaviour change interventions are delivered across a range of substance use treatment settings.

### Strengths and limitations

The current study is being conducted across The Salvation Army residential substance abuse treatment programs. The strength of conducting this type of ‘real world’ research is that it is more representative of actual clinical practice and helps to provide some evidence regarding the feasibility of using these types of interventions as part of ongoing routine care. The research design also includes additional attempts to increase the generalisability of the results by using very inclusive eligibility criteria.

Another strength of the study is that all of the primary and secondary outcome measures used in the study will be collected by assessment officers who are both blind to treatment condition and to the design of the study. Ensuring the blindness of assessment officers to treatment condition has been an issue that has plagued stepped wedge designs. For example, a systematic review examining studies that have used stepped wedge designs found that the articles reported that assessment officers were not blind to treatment condition or they did not specify adequately if assessment officers were blind to condition [33]. The major difficulty with ensuring blindness in stepped wedge designs is that once a study is allocated to the treatment condition, research staff visiting those sites are aware that that site will continue to be allocated to the treatment condition. In the current study we have made the decision to have two sets of assessment officers. One team of non-blind assessment officers visit the residential programs and conduct face-to-face assessments. The primary purpose of these assessment officers is to build a relationship with the participants, introduce the participants to the blind assessment officers over the phone, and to collect background information. The second set of assessment officers, blind to treatment condition and the study design, will be based at the University of Wollongong. We believe that the combination of blind and non-blind assessment officers will help ensure that we maintain a strong relationship with the participants (i.e. promoting follow-up rates) and maintain the scientific credibility of the study.

As with other studies conducted in residential substance abuse treatment settings, a significant challenge is the high rate of unplanned dropout from these units. About 57% of people prematurely leave The Salvation Army programs within the first 3-months of treatment [25], with similar proportions also being reported across the broader literature (see [48]). To help address this concern, Healthy Recovery is delivered over a 5-week period, to maximise the number of groups that participants will complete. A further challenge for the current study will be retaining participants at follow-up. People with alcohol and other substance abuse disorders are traditionally very difficult to follow-up. This is further complicated with residential facilities, as participants often move outside of their local area to attend treatment. Attempts to improve follow-up rates in the current study will include using telephone follow-up, obtaining contact details of significant others to help with locating participants, reinforcing to participants the importance of conducting follow-up and financially compensating participants for the time required to complete the assessments (AUD$20).

## Conclusion

The current study will be the first randomised controlled trial of a healthy lifestyle intervention with a residential substance abuse population. The study seeks to address a significant gap in the multiple health behaviour change literature by examining the effectiveness of implementing an 8-session healthy lifestyle group program within residential substance abuse treatment programs. It is expected that, when compared to the control condition, participants completing Healthy Recovery will demonstrate greater reductions in the number of cigarettes that they smoke, greater increases in fruit and vegetable consumption, and greater increases in the amount of physical activity they engage in. It is anticipated that results from the current study will also help to inform the development and implementation of healthy lifestyle interventions for other marginalized populations that tend to share the same characteristics as people accessing substance abuse treatment services (i.e. mental illness, poverty, homelessness, criminal involvement).
